**PLEASE NOTE:**

**In case of confirmation by the independent medical consultant or in emergency situation (AMG §41 (1)) a deferred informed consent from patient, legal or authorized representative has to be given as soon as possible.**

**If the medical consultant confirms justification of trial participation and the patient or the legal representative thereafter does not give the informed consent, all stored blood samples will be destroyed, but the stored data may continue to be used as described above.**

#### **4.4 Participation in more than one Clinical Trial**

During the verification of the inclusion and exclusion criteria the investigator/his deputy or authorised medical staff of the trial team checks if the patient is currently participating in any other interventional clinical trial(s). Should this be the case, the patient will not be included.

As far as is known, the legal or authorized representative confirms with his/her signature on the consent form that the patient will not simultaneously participate in another interventional clinical trial.

#### **4.5 Statement on the Inclusion of Dependent Individuals**

Due to the emergency situation or the very tight time frame for the treatment of patients during the clinical trial, dependence of the patient on the investigator cannot be ruled out. Not to treat the patient in the study due to a possible dependence on the investigator and to deny him/her a possibly beneficial therapy does not appear to be ethically justifiable. In case of doubt, the patient should not be included in the study by the physician with whom a dependency relationship exists, but by a colleague from the study team, provided that this is feasible in the short time available.

#### **4.6 Rationale for Gender Distribution**

With regard to one German investigation about epidemiological issues (Knake et al. 2001) a gender ratio of 1:2 (female:male) can be expected, but no sufficient data exist in the older age group.

### **5 INVESTIGATIONAL PRODUCT**

#### **5.1 Trial Drugs**

|                     |                                                         |
|---------------------|---------------------------------------------------------|
| Generic Name:       | Valproic acid (VPA)                                     |
| Manufacturer:       | Department Pharmacy of the University Hospital Erlangen |
| Storage conditions: | ≤ 30 °C                                                 |

|                     |                                                         |
|---------------------|---------------------------------------------------------|
| Stability:          | 6 months (Re-Test Date)                                 |
| Generic Name:       | Levetiracetam (LEV)                                     |
| Manufacturer:       | Department Pharmacy of the University Hospital Erlangen |
| Storage conditions: | ≤ 30 °C                                                 |
| Stability:          | 6 months (Re-Test Date)                                 |

The *Investigator Medicinal Product Dossiers* (IMPD) contain detailed information on the quality, manufacture and analysis of the investigational products Valproic acid and Levetiracetam. For clinical information, reference documents are the Summary of medicinal Product Characteristics (Fachinformationen, see 5.5.2) and instructions for use (*Gebrauchsanweisung*) for Valproic acid and Levetiracetam.

All documents mentioned are part of the submission documents.

## 5.2 Packaging and Labelling of the Trial Drug

The investigational products will be manufactured, packaged and labelled by Department Pharmacy of the University Hospital Erlangen according to the current standards of Good Manufacturing Practice (GMP).

The trial drug will be labelled as required by the ICH-GCP Guideline E6 and the German Medicinal Products Act (AMG § 10). The labelling will be in the official language of the country in which the trial takes place.

The master label is part of the documents that will be submitted to the responsible federal authority.

**One** blinded patient-specific trial drug (VAL **or** LEV) with identification number is kept in a separate package, which also contains the unblinding envelope and instructions for use.

The trial medication will not be shipped before all requirements for the start of the clinical trial have been fulfilled according to the internal SOP.

## 5.3 Storage and Handling Requirements

The investigator shall take responsibility for and shall take all steps to maintain appropriate records and ensure appropriate supply, storage, handling, distribution and usage of investigational product in accordance with the protocol and any applicable laws and regulations.

Clinical supplies must be stored in a secure, limited-access location under the storage conditions specified above.

Receipt and dispensing of trial medication must be recorded by an authorised person at the trial site.

Clinical supplies may not be used for any purpose other than that stated in the protocol.

## 5.4 Drug Accountability

After initiation of trial site by the sponsor (executed by the ZKS Leipzig) the delivery of study medication is released. Blinded trial drugs (VAL **or** LEV) will be provided to the trial sites by

Department Pharmacy of the University Hospital Erlangen. The trial drug may only be used within the framework of this clinical trial and in accordance with this trial protocol.

The scope of drug delivery (packages) depends e.g. on the shelf life of the trial medication as well as on recruitment in the further course of the trial.

All shipments will be coordinated by ZKS Leipzig.

Upon receipt of study medication the trial site will fax the medication receipt form to the Department Pharmacy of the University Hospital Erlangen. Trial sites will complete and update a site inventory log about all medication received at the site.

Storage of study medication will strictly follow of the manufacturer's storage recommendation. Temperature logs recorded from min-max thermometers will document the appropriate storage conditions for the respective study medication.

The medical staff at the trial site and the monitor from the ZKS Leipzig evaluate the drug accountability as part of the on-site checks.

For each study subject an individualized drug accountability log will be recorded at trial site.

In the course of the trial unused trial medication and empty packages are collected and destroyed at trial site.

The application of trial drugs is documented in the patient's medical record AND the respective parts of the Case Report Form (CRF). Orderly disposal of trial drugs will be accomplished and documented by the investigator/designated personnel. Storage in the trial sites and administration to patients will be documented by the investigator/designated personnel.

Upon completion or termination of the trial, all unused and/or partially used investigational product will be destroyed at the site per institutional policy provided that procedures for proper disposal have been established according to applicable federal, state, local and institutional guidelines. The investigator is responsible to arrange for disposal of all empty trial drugs and to keep appropriate records of disposal.

The site monitor will assure that a final report of drug accountability is prepared and placed in both the Investigator Site File (ISF) and the Trial Master File (TMF).

## 5.5 Administration of the Study Drugs

### 5.5.1 Procedures

The trial drugs (**either** LEV **or** VPA) shall be administered in a single infusion over **10 minutes**. Therefore, a peripheral intravenous access has to be established according to the clinical standards. The provided formulation includes the maximum possible dosage of 4.5 g LEV **or** 3 g VPA. Always the whole fluid (50 ml) shall be transferred to the syringe for direct use. The perfusor running rate depends on the (estimated) weight.

To patients with a weight of 100 kg or higher the whole 50 ml will be infused, in the other cases the remaining fluid will be discarded.

The start of infusion has to be realized as soon as possible. The infusion has to be stopped in preterm if:

- there are clinical signs of an allergic reaction
- the investigator decides to do so regarding safety issues

In case of cessation of ictal activity before the end of infusion the application has to be finished anyway. The infusion can only be stopped preterm if the investigator rates a risk that justifies this decision.

### The trial drugs will be administered as following:

The dosages for the patients are:

- LEV 45 mg/kg, VPA 30 mg/kg

The perfusor running rate will be adjusted in the following manner:

| Estimated body weight | Running rate (ml/h) |
|-----------------------|---------------------|
| 45-49 kg              | 135                 |
| 50-54 kg              | 150                 |
| 55-59 kg              | 165                 |
| 60-64 kg              | 180                 |
| 65-69 kg              | 195                 |
| 70-74 kg              | 210                 |
| 75-79 kg              | 225                 |
| 80-84 kg              | 240                 |
| 85-89 kg              | 255                 |
| 90-94 kg              | 270                 |
| 95-99 kg              | 285                 |
| 100 kg and more       | 300                 |

### 5.5.2 Dealing with Side-effects

To ensure the appropriate recognition and treatment of complications during the intervention this chapter focusses on possible side-effects of the **i.v.application** of VPA or LEV.

In safety studies the following side-effects of **VPA** have been reported:

- Transient: dizziness, headache, somnolence, taste perversion, nausea, vomiting, injection-site reactions (Devinsky et al. 1995)
- Transient hypotension (Ramsay et al. 2003)
- Asymptomatic hyperammonaemia (DeWolfe et al. 2009)
- Respiratory depression (Trinka et al. 2014)
- Hepatic abnormalities (Trinka et al. 2014)

Case reports also described encephalopathy with or without concomitant hyperammonaemia, acute hepatic failure and acute pancreatitis (reviewed in Trinka et al. 2014).

According to the review (Trinka et al. 2014) about experiences with cumulative 860 patients suffering from various types of SE and treated with i.v. VPA dizziness, thrombocytopenia and mild hypotension are the reported most common side-effects. With regard to the prescribing information (Fachinformation Orfiril® Desitin) the following possible side-effects should also be considered:

- metabolic acidosis, renal failure (frequency unknown)
- Leukopenia, elevation of liver enzymes (often, 1 to 10 of 100 treated subjects)
- Tremor, confusional state (often)
- Bleedings, severe hepatic damage (occasional, 1 to 10 of 1000 treated subjects)
- Severe pancreatic damage (rarely, 1 to 10 of 10.000 treated subjects)

In retrospective case series and safety studies on over 1000 patients including more than 500 patients with SE so far **LEV** has most often been associated with somnolence and sedation (Trinka et al. 2015). In single cases LEV has been associated with delirium (Hwang et al. 2014; Kumar et al. 2014; Foley and Bugg 2010).

Also the following possible side-effects have been reported (Fachinformation Levetiracetam UCB®):

- nasopharyngitis, headache, dizziness (very often, 1 or more of 10 treated subjects)
- agitation, anxiety, hostility, insomnia, depression (often, 1 to 10 of 100 treated subjects)
- nausea and vomiting (often)
- suicidal ideation (occasional)
- thrombocytopenia, leukopenia (occasional)
- cognitive impairment (occasional)
- pancreatitis, severe hepatic or renal damage, encephalopathy (rarely)

The ESET trial (Kapur et al 2019) reports a depressed level of consciousness and respiratory distress as most frequent serious adverse events. The incidence of these events did not differ significantly between the treatment groups (LEV, VPA and fosphenytoin). Numerically depression of consciousness (15 vs. 9) and respiratory depression (10 vs. 8) was more often in the LEV treatment arm than in the VPA treatment arm (Supplement to Kapur et al. 2019).

During the intervention of ToSEE the relevant acute side-effects as hypotension and respiratory depression are recorded by the cardiopulmonary monitoring. In addition at least one member of the trial staff will guard the patient and check his clinical status repeatedly during 60 minutes after the start of the intervention. According to the clinical standard of SE-treatment rescue medication and airway-management shall be provided. The lab analysis before the intervention and after the observation period serves the detection of pre-existent and acute hepatic or renal impairment.

### 5.5.3 Counterindicated/Forbidden Concomitant Medication

According to the potential influence on the plasma level of VPA the following drugs should be avoided during 60 minutes after start of infusion if the responsible investigator approves it justifiable:

- Anticonvulsant drugs: phenobarbital, phenytoin, carbamazepine, felbamate
- Anti-infectives: carbapenem antibiotics, rifampicin, erythromycin, mefloquine, lopinavir, ritonavir
- others: cimetidine, primidone, fluoxetine.

A previous treatment with the anti-infectives mentioned above is **NOT** an exclusion criterion.

### 5.5.4 Overdose and Abuse

None of the two study drugs has known abuse potential. In addition, only one single infusion will be administered. The tolerability of both drugs and of the application regime in elderly and old patients is to investigate. To serve this goal clinical data including adverse events together with the comparison of plasma drug levels before and 60 minutes after the start of infusion will be considered.

## 5.6 Blinding and Unblinding

The trial is a double-blind trial. The trial medication (VAL **or** LEV) will be manufactured by Department Pharmacy of the University Hospital Erlangen (see chapter 5.1). Blinding will also be conducted by the manufacturer.

The randomisation list will be produced by the responsible trial biometrician at the ZKS Leipzig. The original list will contain the allocation of the treatment arm to a corresponding identification number of a study drug package (details to the randomisation process see 8.1.1).

Randomisation will be blinded to the patients and the study site staff. The drugs are both formulated in transparent liquids of the same appearance. Also the running rates of infusion are identical so the blinding can be sustained over the time of intervention.

The unblinding will be implemented by envelopes (sealed and light-proof) provided in the packages. The responsible investigator has to state the time point and reason for unblinding. Also he/she has to confirm in a written form that the unblinding was executed at a time after the end of 15 minutes after the start of the intervention **or** to justify the deviant procedure.

## 6 INDIVIDUAL TRIAL PROCEDURES

### 6.1 Patient Information and Informed Consent

Regarding the addressed disease patients will not be able to provide informed consent at the time of inclusion. As a result, patients are always informed only **after** the study intervention.

The details of the procedures for patients who are not able to provide informed consent in person are described in section 4.3.

In the following, the general procedure for receiving an informed consent is explained. In the case of the ToSEE trial, this will be done if the patient regains the ability to consent or if a legal or an authorised representative is consulted.

In accordance with international guidelines, the informed consent of trial participants will be in writing (written, dated and signed by the person performing the interview referred to below, and by the subject).

The patient's consent must refer explicitly to the collection and processing of health-related data. Therefore the patient, a legal or an authorised representative should be informed explicitly about the purpose of collecting the data and scope of what is to be collected and that personal data, including health related data, will be stored and used for analyses in a pseudonymized form.

Before obtaining informed consent, the potential trial participant, a legal or an authorised representative will receive information regarding the clinical trial in an interview. It will be performed by a qualified medical member of the trial group authorised by the investigator for this task.

The interview has to cover the following items:

- the nature, objectives, benefits, implications, risks and potential inconveniences of the clinical trial
- the expected duration of the subject's participation in the clinical trial
- the information that the patient, a legal or an authorised representative may withdraw his/her consent to participate at any time without giving reasons. The patient is to be informed that in case of revocation of his/her consent, the stored data may be used

further, as may be necessary to

- assess effects of the medicinal product being tested,
  - guarantee that the patient's personal interests are not adversely affected,
  - comply with the requirement to provide complete authorisation documentation.
- potential treatment alternatives
- follow-up measures in case of early termination of the trial for the patient or overall
- the applicable damage compensation system in case of damage to a patient
- the right on data access, rectification and withdrawal of personal data

The trial subject, a legal or an authorised representative will have the opportunity to ask questions at any moment.

The signed original form has to be retained at the trial site, one copy or a second signed exemplar shall be handed out to the patient or the legal or authorized representative.

### 6.1.1 Withdrawal of Informed Consent

Patient (**or** legal or authorised representative) may withdraw their consent to participate at any time without giving reasons. Nevertheless, the patient should be asked for the reason of the premature termination after being informed that he/she does not need to do so. Information as to when and why a patient was registered/ randomized and when he/she withdrew consent must be retained in the documentation.

The patient is to be informed that in case of revocation of his/her consent, the stored data may be used further (according to § 40 lit 2a sublit 3 to 5 German Medicinal Products Act), as may be necessary to

- assess effects of the drug being tested,
- guarantee that the patient's personal interests are not affected adversely,
- comply with the requirement to provide complete authorisation documentation.

Data no longer required for the aforementioned purposes shall be deleted immediately.

## 6.2 Enrolment in the Trial

The inclusion of patients with convulsive SE follows the consideration of the inclusion and exclusion criteria without further diagnostic procedures. The diagnosis NCSE usually requires the confirmation by EEG.

Generally, the local investigator at the trial site may **prescreen** subjects for general participation in the current study on the basis of pre-existing data (diagnosis status epilepticus and age ≥ 65 years). All prescreened patients are listed on a pre-screening list.

**NOTE:** Procedures performed solely for the clinical study can be performed only after inclusion procedures described in chapters 4.3 and 6.1.

At first, general inclusion/exclusion criteria are checked, demographic data are recorded, blood sampling for local laboratory test and if any, further examinations are performed in order to check all inclusion and exclusion criteria - before randomisation (see 6.2.1).

### 6.2.1 Screening

The screening assessments are:

- Assessment of SE status/type using standardized methods
- Note the probable/definite start of SE
- Note the time of the **last** application of benzodiazepines before the intervention
- Assessment of concomitant diseases and medication, as detailed as appropriate
- Further clinical assessment
  - Assessment of vital signs (arterial blood pressure, heart rate, temperature, respiratory rate, estimated body weight) according to clinical standard
- Local lab analysis (EDTA and heparine-plasma and/or serum)
  - Liver function test including alanine aminotransferase, aspartate aminotransferase, gamma-glutamyl-transferase
  - Kidney function test including creatinine, blood urea, glomerular filtration rate,
  - level of valproate, level of levetiracetam,
  - blood count,
  - sodium,
  - blood glucose (if not yet evaluated)

Blood sampling for local lab analysis is performed in parallel with the preparation of the study drug. If the blood sampling could not be completed before the start of the infusion, the procedure must be initiated simultaneously. The time of blood sampling is noted.

Information derived from blood samples taken as part of the SE-treatment in the clinical routine can also be used.

#### **Note!**

Blood sampling and subsequent local lab analysis must not delay start of the patient's treatment.

- Assessment of the GCS,
- perform brief neurological exam: orientation, horizontal extraocular movements, motor drift of both arms and legs, sensation, language
- Obtain the mRS, BI and Home care before admission – if it possible by relatives (see **During 24 hours after T0**)

### 6.2.2 Randomisation

As soon as all assessments required for the final check of eligibility are available, the patient will be randomized directly by the trial site as following:

The allocation of treatment will be done with the help of the packages. The medical staff in the trial sites is compelled to take the set with the lowest ID number ever (see chapter 8.1.1). The identification number of the trial drug package has to be linked to a patient identification number provided on the patient identification list (PIL). Within 24 hours (working day) after the randomisation the patient is registered in the database by the trial site. Following, the eCRF will be provided.

### 6.2.3 Discovery of a Violation of the Eligibility Criteria after the Fact

In general, the violation of eligibility criteria is not a reason for premature withdrawal of the patient from the trial therapy or from the whole trial.

If it is discovered that the patient was not eligible at the time of enrollment, this has to be reported to the Data Management (ZKS Leipzig) as soon as possible. After discussing the best decision for the individual patient and his/her inclusion in the full analysis population between the investigator and the biometrician (e.g. via phone) the ZKS Leipzig informs the investigator /his deputy or authorised medical staff immediately as to what is to be done with the patient. The patient's data will further be recorded.

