|                |                                                                                                                                                                                                                                                                                                                                                                                                                                                                                                                                                                                                                                                                                                                                                                                                                               |
|----------------|-------------------------------------------------------------------------------------------------------------------------------------------------------------------------------------------------------------------------------------------------------------------------------------------------------------------------------------------------------------------------------------------------------------------------------------------------------------------------------------------------------------------------------------------------------------------------------------------------------------------------------------------------------------------------------------------------------------------------------------------------------------------------------------------------------------------------------|
| Biometry       | 
Efficacy: Generalised linear mixed model including randomisation strata as covariate and trial site as random intercept, estimation of odds ratio and rate difference with 95% confidence interval (CI).
 
Description of the primary efficacy analysis and population:
 
Full analysis set (FAS): all patients who received the trial medication will be analysed as randomized (intention-to-treat principle)
 
Safety: Frequencies with 95% CI of complication rates and (S)AEs
 
Secondary endpoints: Event rates (incl. 95% CI), chi test, time to cessation of SE by time-to-event methods, (generalized) mixed linear models for longitudinal analyses as well for the other endpoints (e.g. questionnaire scores) similar to the primary endpoint.
 |

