## 6.4 Premature Termination of the Trial

Because the endpoint is assessed until 60 minutes only few patients will terminate the study prematurely: This may be patients who or whose representatives withdraw a former informed consent.

The primary statistical analysis follows the intention to treat principle as closely as possible. For a valid analysis, it is of great importance to minimise the rate of drop-outs. Therefore, in patients who do not withdraw their consent, all trial visits shall be performed as scheduled.

In case of premature termination of trial, it is necessary to document the date (as exactly as possible), the reason of termination and the current condition of the patient. Therefore, the eCRF "End of study (ES)" has to be completed for each patient. Data entry to this eCRF page will trigger an automatic report to the responsible trial team members at the ZKS Leipzig.

The "End of study"- eCRF routinely contains the following data:

- Date of individual end of trial
- Reason for trial termination

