#### Randomisation procedure

Randomisation lists are created by statistical software. Blocks of randomly chosen length are created as realisations of random samples and stringed together to a list.

ZKS Leipzig delivers one randomisation list per centre each to the central pharmacy Erlangen. Beginning with the first entry in the randomisation list, the staff of the pharmacy packs medication kits for one patient each. Every kit is labelled by a consecutive ID number and contains a sealed opaque envelope revealing the information about the medication. A pre-defined number of kits are packed into a package and are sent to the trial sites. The medical personal in the trial sites is obliged to take the set with the lowest ID number. Treatment failure is defined as clinical evidence of epileptic activity and / or persistent electroencephalographical ictal activity consistent with NCSE according to the Salzburg criteria 15 minutes after the initiation of intervention or recurrence of ictal activity (in case of NCSE return of EEG patterns to baseline status after initial treatment response) during the further 45 minutes observing period which leads to immediate unblinding of medication. In case of treatment success, drug therapy will be unblinded after 60 minutes to ensure appropriate further treatment (see Figure 1). The investigator is responsible that the envelope is not opened before.

Every trial site is equipped first with a start package of fixed number of medication sets. The size of further packages may be adapted in accordance to the accrual of the trial sites.

The trial sites inform the ZKS about every included patient and transfer the medication ID. Matching the randomisation list with the correspondent list from the central pharmacy Erlangen, the ZKS is able to oversee the randomisation process and the medication logistics.

By study design most of the effects in secondary endpoints cannot be unequivocally attributed to the trial medication. Regarding the parameters, they are not susceptible to biased evaluation either. To minimize bias arising from evaluation of EEG-patterns, EEG evaluation trainings shall be performed. Each trial site will be equipped with working instructions to ensure homogeneity of procedures. These working instructions will cover:

1. The preparation of the intervention
2. The procedures during 60 minutes after the start of intervention
3. The procedure of uploading the EEG data
4. The report of AEs.

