#### Blinding

Patients as well as treating physicians are blinded until 60 min after initiation of the infusion at the latest. After 60 minutes at the latest, the medication is unblinded in order to be able to decide on further treatment.

For unbiased evaluation of the primary endpoint final EEG is assessed by two expert raters (EEG reference board) blinded to treatment arm allocation.

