## 8.5 Statistical Methods

### 8.5.1 Analysis Population

Primary analysis bases on the full-analysis set (FAS), that is, all patients who received trial medication. The patients are analysed in the arm they were allocated independently from the actual treatment. This follows the intention-to-treat principle.

The per-protocol set (PPS) consists of all patients who pass through the study according to the TP. Patients for whom the diagnosis NCSE was not confirmed by the central EEG review will be excluded from the PPS. Per-protocol analysis is done as a sensitivity analysis. However, if PPS is 95% or more from the FAS, a PP analysis is dispensable.

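### Section 6.2.3 leaves an ineligible patient's place in the full analysis set to case-by-case discussion, contradicting the fixed definition in 8.5.1 and permitting exclusions that may depend on arm and outcome

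*Protocol*

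**What the plan says.** Two parts of the protocol govern the same patients.

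- **Section 6.2.3** covers a patient found after enrolment not to have been eligible. It starts from the position that "the violation of eligibility criteria is not a reason for premature withdrawal of the patient from the trial therapy or from the whole trial". The case is reported to data management, and the site is told what to do "After discussing the best decision for the individual patient and his/her inclusion in the full analysis population between the investigator and the biometrician"; a telephone call is given as an example of how. It closes with "The patient's data will further be recorded".
- **Section 8.5.1** states: "Primary analysis bases on the full-analysis set (FAS), that is, all patients who received trial medication". Patients are analysed in the allocated arm whatever they actually received. The synopsis gives the same rule, and section 6.4 adds: "The primary statistical analysis follows the intention to treat principle as closely as possible".

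Four other places bear on who knows what, and when.

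- **Section 8.1.1, Blinding:** "After 60 minutes at the latest, the medication is unblinded in order to be able to decide on further treatment".
- **Section 8.1.1, Randomisation procedure:** treatment failure is an event "which leads to immediate unblinding of medication". Sites also report the medication number of each included patient to the trial centre.
- **Section 5.6:** the trial biometrician produces the list that links package numbers to arms.
- **Section 6.2.2:** the site has 24 hours (working day) after randomisation to register the patient in the database.

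**The concern.** If FAS membership followed 8.5.1, section 6.2.3 would have nothing to discuss: a patient who received trial medication is in. By making inclusion a topic of individual discussion, 6.2.3 implies that a treated patient can be left out of the set on which the primary test is run. It does not say on what grounds, on what information, or that the people deciding must be blind to arm and outcome.

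In most trials a loose clause like this would be softened by blinding. Here blinding ends within the hour for every patient, and earlier for failures. If even a few exclusions lean with arm and outcome, the comparison is no longer protected by randomisation: the odds ratio is biased and the 5% level is not held.

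**Working it through.** **Step 1. The two rules side by side.** Section 8.5.1 has one condition for the FAS, receipt of trial medication, and no eligibility condition. Section 6.2.3 adds a second, undefined condition for patients found ineligible. Both cannot hold. The sentences in 6.2.3 on not withdrawing the patient and on continuing to record data concern therapy and follow-up; they do not say which analysis set the patient belongs to.

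**Step 2. What is known at the time.** The infusion lasts 10 minutes and the observation period for the primary endpoint ends at 60 minutes (sections 3.4 and 8.2.1). The arm is disclosed by then, or sooner after failure. A report made after the first hour, and certainly one made around database registration, comes from an investigator who knows the arm and has seen the response. The biometrician holds the allocation list, although the protocol does not say it would be consulted.

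**Step 3. The plan's own sample size.** Inputs from section 8.4: 60% vs 47% success, two-sided 5%, 80% power. With the unpooled normal formula,

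n per arm = (1.960 + 0.842)² × (0.60×0.40 + 0.47×0.53) / 0.13² = 227.15,

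so 2 × 227 = 454, as stated. The sample size is not in dispute; it supplies the 227 per arm used below.

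**Step 4. Size of the possible bias.** Assumptions: no true difference; success p = (0.60 + 0.47)/2 = 0.535 in both arms; 227 per arm; a share e of patients in each arm ineligible, with the same success rate as the rest. The protocol gives no value for e, so 2%, 5% and 10% are shown. The test is the two-sided 5% two-proportion z test, a simplification of the planned mixed model with centre as a random effect.

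- All ineligible failures dropped from arm A: p₁ = p / (1 − e(1 − p)), n₁ = 227(1 − e(1 − p)).
- All ineligible successes also dropped from arm B: p₂ = p(1 − e) / (1 − ep), n₂ = 227(1 − ep).
- Rejection probability = Φ((d − 1.96·SE₀)/SE₁) + Φ((−d − 1.96·SE₀)/SE₁), where d = p₁ − p₂, SE₀ is the pooled and SE₁ the unpooled standard error.

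Worked case, e = 5%, both arms:

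- p₁ = 0.535/0.97675 = 0.5477 and n₁ = 221.7 (5.3 failures removed).
- p₂ = 0.50825/0.97325 = 0.5222 and n₂ = 220.9 (6.1 successes removed).
- d = 0.0255, SE₀ = SE₁ = 0.0474.
- Rejection probability = Φ(−1.422) + Φ(−2.499) = 0.0775 + 0.0062 = 0.0837.

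| Ineligible | Failures dropped in one arm: difference, OR, type I error | Successes dropped in the other arm too (worst case): difference, OR, type I error |
|---|---|---|
| 2% | 0.5 points, 1.02, 5.1% | 1.0 points, 1.04, 5.5% |
| 5% | 1.3 points, 1.05, 5.8% | 2.6 points, 1.11, 8.4% |
| 10% | 2.6 points, 1.11, 8.5% | 5.2 points, 1.24, 19.3% |

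If only half of those patients are dropped, in both arms, the type I error is 5.1%, 5.8% and 8.4%. If exclusion is unrelated to arm and outcome, the expected difference stays zero and there is no bias of this kind.

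**The case against.** The strongest reply is that the governing rule is already right. Section 8.5.1, the synopsis and section 6.4 all set an intention-to-treat approach without discretion, and 6.2.3 is a conduct section that names no ground for exclusion. A reader might infer from 6.2.3 that the primary analysis is not intention-to-treat. The documents do not support that: they contain a contradiction, and 6.2.3 permits a departure without ordering one.

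Three other strong readings also fail.

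- **That arm and outcome are known in every such discussion.** A violation found in the first hour in a responding patient may precede unblinding. In nonconvulsive cases the primary outcome is read by an external EEG board blinded to treatment (sections 8.1.1, 8.2.1 and 11), so the investigator sees the bedside course, not the adjudicated result. The accurate word is usually.
- **That late discovery will be common.** No rate is given. Ten of the fifteen exclusion criteria (3 to 8 and 12 to 15) turn on what was known, or in criterion 3 known or suspected, at enrolment, so a fact learned later generally breaches none of them. Others do not carry that word, such as prior treatment of the episode with other antiepileptic drugs or sedatives, or the benzodiazepine time window, so late findings are possible.
- **That every foreseeable late finding is exposed.** Nonconvulsive status not confirmed by central EEG review is already sent to the per-protocol set by 8.5.1, on blinded assessment.

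What remains is that nothing elsewhere cancels the clause. Section 13.1 has violations discussed with the biometrician before the database is closed, again with no blinding condition. A statistical analysis plan could choose between the rules, but the conflict is in the protocol text itself.

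**Conclusion.** The point holds as a contradiction. Section 6.2.3 makes FAS membership of an ineligible patient discretionary, while 8.5.1 and the synopsis make it automatic on receipt of trial medication. Because of early unblinding, the discretion would usually be used with the arm and bedside response known, so exclusions from the primary analysis could depend on both.

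The likely size is small if few patients are ineligible: at most about 1 percentage point and a type I error of 5.5% at 2%. It becomes material only when ineligibility is more frequent and exclusion is selective; the 8.4% and 19.3% figures for 5% and 10% are worst cases with perfectly directed exclusion in both arms. All of these rest on assumed ineligibility shares, no true effect and the simplified test. They show what the clause allows, not what is expected to happen. The wording should still be corrected, because it concerns the primary analysis set and the correction costs almost nothing.

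**What to change.** In section 6.2.3, delete the words on inclusion in the full analysis population. State instead that every patient who received trial medication stays in the FAS as defined in 8.5.1, whatever eligibility violation is found later. Add that eligibility violations can affect only the per-protocol set, with membership fixed before database lock without reference to allocation or outcome. Discussion between site and trial centre about the individual patient can continue, but not about the FAS.

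The cost is one or two sentences in the protocol, carried into the statistical analysis plan. No extra data are needed. The target of 454 analysed patients and the two-sided 5% level stay as they are.
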